#### Primary outcomes

The primary outcomes are *recidivism* and *self-sufficiency*. Recidivism will be scored from official judicial records. These records provide information about the type, frequency and severity of offenses as well as time to offenses [82]. The observation period will begin at T0. We will gather data on official arrests from 6 months before baseline as well to obtain insight into the history of registered offenses. Additionally, self-reported delinquency will be measured at T0, T2 and T3 by 29 items of the *Self-report Delinquency Scale* (SRD) [83]. This questionnaire consists of a total delinquency score that can also be divided into five subscale scores: public order offenses, property crimes, violent crimes, drug-related crimes and owning illegal weapons. Participants are asked if they have committed specific offenses (“yes” or “no”) as well as how often they have done so in the last 6 months.

Self-sufficiency will be measured with the Dutch version of the Self-Sufficiency Matrix (SSM-D), based on the American version of the SSM [84] and adapted to, and validated for, the Dutch population [39, 85, 86]. Self-sufficiency is being able to create an acceptable level of functioning on the important domains of life [87]. The SSM-D consists of 11 life domains: income, daily activity, housing, mental health, physical health, addiction, general life skills, social network, community involvement and justice. A trained researcher allocates, based on the information of the participant, a score between 1 (acute problems) and 5 (completely self-sufficient) to each SSM domain indicating the degree of self-sufficiency. The SSM is administered at T0, T1, T2, T3 and start of intervention. A compounded, overall self-sufficiency score will be developed for the primary analysis in collaboration with the developers of the SSM-D (Public Health Service in Amsterdam).

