### Statistical analysis

Primary analyses will be conducted in accordance with the *intention-to-treat principle* (ITT) [75, 109–112]. Additionally, a second analysis will be performed in which only participants who actually started with the intervention are included. By conducting these two analyses, we will be able to measure both the effectiveness of *assigned* treatment and *actual* treatment which could provide valuable information for clinical practice [113].

The outcomes at T3 will be used to determine the main effects of DNK compared to CAU. Missing data at T3 will be imputed according to the multiple imputation approach, for which we will use LISREL 8.8. This approach follows the expectation maximization algorithm (maximum likelihood estimation) [114, 115]. The primary and secondary continuous outcome measures (i.e., self-reported recidivism, self-sufficiency, quality of life, psychopathology, cognitive distortions and substance use) will be analyzed with independent samples *t* tests, using treatment condition (DNK versus CAU) as independent variable and the outcome measures as dependent variables. The effect sizes are computed as Cohen’s *d*, based on adjusted means and standard deviations. The categorical outcome measure *work/school* will be examined with a chi-square test. An odds ratio will be calculated as effect size. To obtain insight into the *time to recidivism* (i.e., recorded delinquency) survival curves will be drafted. To examine the differences in registered recidivism between DNK and CAU, a Cox regression analysis will be conducted. The hazard ratio will be used as effect size.

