To gain more insight into the possible differences between DNK and CAU in the development of the primary and secondary treatment outcomes up to and including T3, additional analyses will be conducted by means of mixed-model analyses for the continuous outcome measures (i.e., recidivism, self-sufficiency, quality of life, psychopathology, cognitive distortions and substance use) and Generalized Estimating Equations (GEE) for the categorical outcome measure *work/school*. In these analyses, the outcome data of T0, T2 and T3 will be included. T1 data are excluded from the analyses since T1 is an additional assessment point to measure treatment characteristics and, therefore, not all primary and secondary outcomes are included at T1. In the mixed-model analysis *treatment condition* and *time* (i.e., the assessment point: T0, T2 or T3) will be set as fixed factors, and the participants as a random effect. By analyzing the interaction between treatment condition and time, differences between both groups in development over time can be examined. If the overall interaction is significant, post-hoc analyses will be conducted to investigate at which time point the differences can be found. A similar analysis will be conducted with GEE, using an unstructured correlation matrix to account for within-subject correlations due to repeated measures.

Subsequently, moderator analyses will be carried out by the addition of potential moderators as covariates (in case of continuous variables) or as factor (in case of the categorical variable work/school) to the abovementioned mixed-model and GEE analyses. A three-way interaction between treatment condition, time and moderator will give insight into the influence of a moderator on the development in outcome between DNK and CAU. Post-hoc analyses will be carried out if the model appears to be significant. Moderators regarding registered recidivism will be examined with Cox regression analyses (a two-way interaction between treatment condition and the moderator).

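### The main T3 test of the six continuous outcomes is a t test that uses no T0 value, yet Cohen's d is to rest on adjusted means that this test does not produce

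*Protocol article*

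**What the plan says.** The Statistical analysis section fixes the time point of the main analysis: "The outcomes at T3 will be used to determine the main effects of DNK compared to CAU". The outcomes it treats as continuous are "self-reported recidivism, self-sufficiency, quality of life, psychopathology, cognitive distortions and substance use". The first two belong to the primary outcomes and the other four are secondary. All six are to be compared by "independent samples *t* tests, using treatment condition (DNK versus CAU) as independent variable and the outcome measures as dependent variables". The next sentence says that Cohen's d is "based on adjusted means and standard deviations", without naming a covariate or an adjusting model.

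A T0 value is planned for every one of the six. The Primary outcomes section states that "self-reported delinquency will be measured at T0, T2 and T3 by 29 items" of the delinquency scale and that "The SSM is administered at T0, T1, T2, T3 and start of intervention". Table 1 marks T0 for the SRD, SSM-D, MANSA, ASR, HIT and MATE. The Design section places randomisation after T0.

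T0 is used in one other place, the mixed models that the article calls additional: "In these analyses, the outcome data of T0, T2 and T3 will be included". There it is one of the repeated outcomes in a condition-by-time analysis.

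**The concern.** There are two separate problems.

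First, the stated test and the stated effect size do not fit together. A t test on condition alone compares raw arm means. Adjusted means need a model with at least one covariate, and none is given for the main analysis. As written, the reported p value and the reported d for two primary outcome measures would come from different models. The choice of covariates behind d would stay open until the data are seen.

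Second, the main test leaves out the most obvious prognostic variable for each outcome, which is the same measure taken before randomisation. The Background section attributes earlier null results partly to small samples and says this trial aims to avoid a lack of power. The Discussion expects an active control to shrink the effect. Setting aside precision that costs nothing to obtain works against both statements.

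**Working it through.** **Inputs from the protocol article.** Power analysis: about 100 per arm, alpha .05 (sidedness not stated), power .80, a small to medium effect with no number given, about 34% dropout, 150 per arm, 40% run-in loss, 500 recruited. Design: 1:1 allocation after T0.

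**Assumed.** Two-sided alpha. T0–T3 correlation r between 0.2 and 0.7, since the article gives none.

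**Step 1: reproduce the stated size.** Solving the two-sample t test for 100 per arm, two-sided .05 and 80% power gives d = 0.398 (normal approximation: √(2/100) × (1.960 + 0.842) = 0.396). That lies within small to medium. The inflation steps follow: 100/(1 − 0.34) = 152 against the stated 150, which leaves 150 × 0.66 = 99; and 300/(1 − 0.40) = 500. The planned size therefore fits an unadjusted two-group comparison.

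**Step 2: adjust for T0.** In an ANCOVA the residual variance is multiplied by 1 − r². With outcome SD 1 and n = 100 per arm:

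- power = Φ( 0.398 / (√(1 − r²) × √(2/100)) − 1.960 )
- detectable difference at 80% power = 0.396 × √(1 − r²)
- n per arm for the original power = 100 × (1 − r²)

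Worked case, r = 0.5: √0.75 = 0.866; 0.398/(0.866 × 0.1414) = 3.25; 3.25 − 1.96 = 1.29; Φ(1.29) = 0.90.

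| r (assumed) | 1 − r² | Power | Detectable difference (SD) | n per arm |
|---|---|---|---|---|
| 0 (t test) | 1.00 | 0.80 | 0.396 | 100 |
| 0.2 | 0.96 | 0.82 | 0.388 | 96 |
| 0.3 | 0.91 | 0.84 | 0.378 | 91 |
| 0.5 | 0.75 | 0.90 | 0.343 | 75 |
| 0.7 | 0.51 | 0.98 | 0.283 | 51 |

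A simulation with 4000 runs per value of r agrees. Power of the t test against ANCOVA was 0.80 against 0.83 (r = 0.3), 0.78 against 0.89 (r = 0.5) and 0.80 against 0.98 (r = 0.7).

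**Step 3: chance imbalance at T0.** With 100 per arm the standard error of the T0 difference is √(2/100) = 0.14 SD. A T0 difference of 0.2 SD or more in either direction is 0.2/0.1414 = 1.41 standard errors, which arises by chance in about 16% of trials for any one outcome. Given such a difference and r = 0.5, the raw T3 difference is shifted by 0.5 × 0.2 = 0.10 SD. ANCOVA removes that shift, conditional on the observed baseline.

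**Step 4: why the SD behind d must be named.** The same adjusted difference of 0.398 raw SD gives d = 0.40 if divided by the raw SD. Divided by the residual SD it gives 0.398/0.866 = 0.46 at r = 0.5, or 0.398/0.714 = 0.56 at r = 0.7.

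**The case against.** The best defence is that the planned test is sound. Allocation is random and follows T0, so an unadjusted T3 comparison has the right type I error, and Step 1 shows that the sample was sized for it. T0 is not lost from the plan either, because the mixed models include it. The precision gain depends on a correlation the article does not supply. At r = 0.2 to 0.3 it is only 2 to 4 percentage points of power. For self-sufficiency, the Study sample section restricts several SSM-D domains at entry, which may lower r. All of this stands. It limits the size of the point but leaves the mismatch between the t test and the adjusted means untouched. The mixed models do not resolve that mismatch, because they are labelled additional and reach a T3 contrast only post hoc.

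A reader might infer several stronger claims that the article does not support:

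- **The t test is biased by baseline imbalance.** A chance imbalance is sampling error, already covered by the t test's standard error. The 0.10 SD in Step 3 is a conditional shift in an illustrative case, not a bias of the method.
- **Adjusting for T0 would repair the exclusion of people who do not return after the run-in period.** It would not, because selection on unmeasured factors remains. That exclusion is a separate matter.
- **The Cox model must carry prior arrests because** "We will gather data on official arrests from 6 months before baseline as well". The article uses criminal history as a moderator in Cox regression, and a covariate list for the main Cox model may properly sit in a fuller plan.
- **Self-reported delinquency needs a count model.** That is a different question about its distribution, and such a model would not yield Cohen's d.

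**Conclusion.** The point holds as one of internal consistency and efficiency, not of validity. The inconsistency is certain and needs no assumption: the named test cannot supply the adjusted means on which d is to be based, and no other model is defined for the main analysis. The loss of efficiency is certain in direction for any non-trivial correlation, but its size is uncertain. It ranges from 2 percentage points of power at r = 0.2 to about 18 at r = 0.7. These figures assume two-sided alpha, d of about 0.40, and 100 per arm with full information. Multiple imputation would change the effective number somewhat. The scope is the six continuous outcomes only; registered recidivism (Cox regression) and work/school (chi-square) are not affected.

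**What to change.** Replace the t tests in the Statistical analysis section with a linear model (ANCOVA) for each continuous outcome at T3, containing treatment condition and the T0 value of the same measure. Apply it to the multiply imputed intention-to-treat data. For self-sufficiency, use the T0 score and not the score taken at the start of the intervention (Ts), because Ts falls after randomisation. Take the p value, the confidence interval and the adjusted mean difference from this one model. State which SD divides the adjusted difference to give Cohen's d.

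The cost is a few sentences of wording. No new data, visits or participants are needed. The Trial status section says that data collection runs until January 2018 and that effects are unknown until then, so the article leaves room to make the change before results are seen.

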### Study sample

Young adults are eligible for participation in the trial if they meet the following inclusion criteria: (1) they are male, (2) they are aged between 18 and 27 years, (3) they have sufficient knowledge of the Dutch language to understand the study procedure and the questionnaires and (4) they meet the criteria of a *multi-problem* young adult according to the Self-Sufficiency Matrix – Dutch version (SSM-D; see “Instruments” for an extended description and clarification of the scores), namely: (a) a score of 1 or 2 on the domains Income and Daily activities, (b) a score of 1, 2 or 3 on at least one of the following domains: Addiction, Mental health, Social network, Justice and (c) a score of 3, 4 or 5 on the domain Physical health. The multi-problem definition is based on the SSM-D profile of DNK participants who had an intake at the social welfare agency in 2012.

When a young adult meets the abovementioned criteria, the researcher and youth coach will jointly verify whether the young adult meets one of the following exclusion criteria: (1) treatment or day program has already started before intake, (2) the participant is referred to a specific institution for direct intermediation to work, (3) the participant has an intermediate level of vocational education (in Dutch: MBO, level 4) or higher, (4) the participant already is, or has been, in treatment at DNK, (5) the participant will not get assistance from the social welfare agency due to practical issues (e.g., he has almost reached the age of 27 years) and (6) the participant has very specific psychopathology or an indication of a very low IQ level and, therefore, requires specialized care.

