### Power analysis

Power calculations (conducted with G* power) indicate that approximately 100 multi-problem young adults per treatment condition (assuming an alpha of .05, a power of .80, and a small to medium effect size) are sufficient to detect a difference in treatment effects at T3. However, we expect some dropout after referral to the interventions. James and colleagues [78], for example, had to deal with a dropout rate of approximately 34% (p. 1163) between pre and posttest (i.e., 9 months after baseline) in a group of juvenile and young adult offenders. Therefore, we aim to include 150 participants per treatment condition. To include 300 multi-problem young adults in total in our study, we need to recruit 500 participants at the social welfare agency as the estimated dropout rate here within the effort period is 40% (p. 9) [71].

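### The main Cox analysis of registered recidivism names no adjustment for prior offending, which forgoes some precision and counts first-ever offences as recidivism

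*Protocol article*

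**What the plan says.** All references are to the Protocol article.

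- **Main analysis** (Statistical analysis): "To examine the differences in registered recidivism between DNK and CAU, a Cox regression analysis will be conducted". The hazard ratio is the effect size. The same paragraph explains time to recidivism as time to recorded delinquency. No covariate or stratum is named for this model.
- **Eligibility** (Study sample): besides the other criteria, a man needs "a score of 1, 2 or 3 on at least one of the following domains: Addiction, Mental health, Social network, Justice". Justice is one of four alternatives, so entry through Addiction, Mental health or Social network alone is possible.
- **Event window** (Primary outcomes): counting starts at T0 for everyone, with no condition on an earlier offence. The article adds: "We will gather data on official arrests from 6 months before baseline".
- **Criminal history** (Potential moderators: participant characteristics): lifetime offending is taken from the SRD. Age at first offence and offence history are taken from official data.
- **Use of criminal history** (Background, Aims of the study, Statistical analysis): it is a potential moderator. For registered recidivism, moderators enter Cox models as an interaction with treatment, after the main analysis.

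**The concern.** Past offending is likely to predict later offending, and the entry criteria allow men with and without a record into the same comparison. If a strong prognostic factor is left out of a Cox model, a non-null treatment hazard ratio moves toward 1 and power falls, even with perfect randomisation. The Background blames small samples for earlier null findings on registered recidivism and promises to avoid that problem. The Discussion expects smaller effects against an active control. Precision available from data already collected therefore matters.

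There is also a question of naming. The event is any recorded offence after T0. For a man with no earlier offence that is a first offence, not a repeat one, and a claim that DNK reduces recidivism would rest partly on such events.

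**Working it through.** **1. The plan's own sample size.** Power analysis gives "approximately 100 multi-problem young adults per treatment condition", "assuming an alpha of .05, a power of .80, and a small to medium effect size". The effect size has no number. A two-sided two-sample t test needs 99.08, so 100, per arm at d = 0.40, and power at 100 per arm is 0.804. At d = 0.3 it needs about 175, and at d = 0.5 about 64. The figure therefore reproduces as a comparison of means at d of about 0.40 (one-sided, d = 0.35 gives 101 and also fits). The article cites a "dropout rate of approximately 34% (p. 1163) between pre and posttest": 100/(1 - 0.34) = 152, close to the 150 stated ("we aim to include 150 participants per treatment condition"). For recruitment, 300/(1 - 0.40) = 500, as stated ("we need to recruit 500 participants at the social welfare agency"). No event count or hazard ratio is given for the Cox outcome.

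**2. Events needed, for context.** At an assumed hazard ratio of 0.60, two-sided alpha 0.05 and 80% power:

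- Schoenfeld: 4(1.96 + 0.84)²/(ln 0.60)² = 121 events.
- Freedman: (1.96 + 0.84)² × (1.60/0.40)² = 126 events.

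**3. Cost of leaving out prior record.** Inputs from the article: 1:1 allocation, 150 per arm, 14 months from T0. Assumptions: records available for all 300 men; exponential times; treatment hazard ratio 0.60 given prior record; share π with a prior record of 50% or 70%; prior-record hazard ratio θ of 2, 3 or 5; control-arm risk at 14 months of 30% or 50%. The baseline hazard λ solves 1 - [π·exp(-14λθ) + (1 - π)·exp(-14λ)] = control-arm risk. There were 2000 simulated trials per row, each analysed with treatment alone and with treatment plus prior record.

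| π | θ | Control risk | Events | HR unadj. | HR adj. | Power unadj. | Power adj. | Gain (points) |
|---|---|---|---|---|---|---|---|---|
| 50% | 2 | 30% | 74 | 0.601 | 0.596 | 57.5% | 57.8% | 0.3 |
| 50% | 2 | 50% | 127 | 0.605 | 0.595 | 80.6% | 82.9% | 2.3 |
| 50% | 3 | 30% | 74 | 0.608 | 0.597 | 55.0% | 58.6% | 3.6 |
| 50% | 3 | 50% | 128 | 0.618 | 0.596 | 76.4% | 82.2% | 5.8 |
| 50% | 5 | 30% | 75 | 0.627 | 0.604 | 50.3% | 57.2% | 6.9 |
| 50% | 5 | 50% | 129 | 0.643 | 0.599 | 69.1% | 81.0% | 11.9 |
| 70% | 2 | 30% | 74 | 0.593 | 0.590 | 57.2% | 58.2% | 1.0 |
| 70% | 2 | 50% | 126 | 0.606 | 0.600 | 79.6% | 81.1% | 1.5 |
| 70% | 3 | 30% | 74 | 0.603 | 0.597 | 55.6% | 57.4% | 1.8 |
| 70% | 3 | 50% | 128 | 0.612 | 0.598 | 78.8% | 82.9% | 4.1 |
| 70% | 5 | 30% | 74 | 0.604 | 0.594 | 56.8% | 59.7% | 2.9 |
| 70% | 5 | 50% | 128 | 0.619 | 0.594 | 75.6% | 81.6% | 6.0 |

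**4. Validity under no effect.** With treatment hazard ratio 1, π = 70%, θ = 3 and 50% control risk, type I error was 4.6% unadjusted and 4.8% adjusted.

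**5. Size of the drift.** The largest is ln(0.643/0.60) = 0.069. With 129 events the standard error of the log hazard ratio is about 2/√129 = 0.176, so the drift is about 0.4 of a standard error.

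**6. More extreme contrasts** (500 trials each, same hazard ratio and arm size, stratified Cox). Reading the offence rates as control-arm risks, the implied prior-record hazard ratio is ln(1 - p₁)/ln(1 - p₀).

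- 60% with a record, offence rates 40% versus 10%: 0.511/0.105 = about 4.8; power 48.6% to 53.6%.
- 60% with a record, 60% versus 10%: 0.916/0.105 = 8.7; power 60.2% to 70.4%.
- 50% with a record, 60% versus 5%: 0.916/0.051 = 17.9; power 45.6% to 62.0%, unadjusted hazard ratio 0.645.

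Gains of 10 to 16 points at these settings need prior-record hazard ratios of about 9 to 18.

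**The case against.** **The article does not say that the model contains treatment only.** It lists no predictors for the Cox model. It is a condensed text, and Design refers to a fuller protocol held by the ethics committee. This stands as a limit: a covariate may be named there. The point is that the comparison as published can be improved, and that its event is loosely named.

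**Prior offending is not ignored.** A reader might infer that it is, but the documents do not support that. It is measured from two sources and is a planned moderator, in Cox models for this outcome. What remains is that an interaction fitted later does not make the main estimate more precise.

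**The unadjusted analysis is not wrong.** A reader might infer a biased or invalid test from a hazard ratio that moves toward 1. Randomisation protects the test, and the simulated type I error agrees. The shift reflects the difference between a marginal and a conditional hazard ratio. The marginal one is a legitimate target, and it suits a pragmatic trial.

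**The naming problem is modest.** Both Aims of the study and Statistical analysis equate recidivism with delinquency, so a careful reader knows what is counted. The Discussion, however, speaks of time to relapse, which does not fit men without an earlier offence.

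**Conclusion.** The point holds as one of efficiency and naming. As described, the main Cox comparison leaves out a baseline factor that is already collected and probably prognostic, and its event includes first-ever offences. In the scenarios in the table the cost is 0-2 power points at a prior-record hazard ratio of 2, 2-6 at 3 and 3-12 at 5, with an unadjusted hazard ratio of at most about 0.64 against 0.60. These figures rest on the assumed treatment effect, share of men with a record, event risk and prognostic strength. The article gives none of these, so how mixed the sample really is remains unknown.

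A reader might also infer that adjustment would rescue the power of this outcome. It would not: at 30% control risk, adjusted power stays between 57% and 60%, because about 74 events fall short of the 121 to 126 needed at a hazard ratio of 0.60.

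**What to change.** - Pre-specify prior registered offending at T0 (yes/no) as a covariate or stratum in the main Cox model. Keep the unadjusted hazard ratio as a sensitivity result.
- Take it from the full official history (age at first offence, history of offences), not from the 6-month arrest look-back in Primary outcomes. Six months cannot separate first from repeat offenders. State how the two sources relate.
- Name the event the first registered offence after T0. As a secondary result, report the hazard ratio in men with a prior record, as recidivism in the strict sense.

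The cost is a few lines in the analysis plan. The data are already being collected, and no participants or visits are added. Trial status reports the intervention effects as unknown until data collection ends in January 2018, so at the time of the article the choice could still be made before results were seen.

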Multi-problem young adults aged between 18 and 27 years will be recruited after their first interview at the social welfare agency in Rotterdam. After informed consent is obtained, baseline measurement (T0) will take place. After T0, the random assignment (with a ratio between DNK and CAU of 1:1) will be carried out by the first author. The random allocation is determined via an online computer program for randomization (www.random.org). Subsequently, the randomization numbers will be kept in sealed envelopes at the social welfare agency. During the baseline measurement the participant, researcher and youth coach will still be blind to the treatment condition. The first author will inform the youth coach about the outcome of the randomization. Only at the second interview will the young adult be informed by the youth coach about the assignment to the treatment or control condition. During the phase between the first and second interviews, the so-called statutory effort period, no intervention takes place. Only the participants who return for a second interview can be referred to an intervention. Therefore, participants who do not return within the run-in period will be excluded from the analyses. In this way, the statutory effort period is considered as a run-in period [74, 75] to deal with the estimated dropout rate of approximately 40% (p. 9) during this period [71]. Although some researchers have pointed out that a run-in period may influence the generalizability of the results [74, 76], it will improve the internal validity – the primary condition for valid outcomes – of our study [77]. Of the subjects who will be excluded during the run-in period, data will be collected at the follow-up measurements to compare the outcomes of the included and excluded groups and to incorporate this in generalizations from the study [74]. Figure 1 shows the flowchart of this study and Fig. 2 shows the SPIRIT schedule of enrollment, interventions and assessments.

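### The additional mixed model gives each arm its own T0 mean although T0 precedes randomisation, so its treatment × time test is less precise than a model adjusted for T0

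*Protocol article*

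**What the plan says.** The Statistical analysis section of the protocol article decides effectiveness at the last visit: "The outcomes at T3 will be used to determine the main effects of DNK compared to CAU". For continuous outcomes that is an independent-samples t test.

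A second layer follows: "additional analyses will be conducted by means of mixed-model analyses for the continuous outcome measures". Its data are specified: "In these analyses, the outcome data of T0, T2 and T3 will be included". So are its terms: treatment condition and time ("i.e., the assessment point: T0, T2 or T3) will be set as fixed factors, and the participants as a random effect"). The arm comparison is the interaction: "By analyzing the interaction between treatment condition and time, differences between both groups in development over time can be examined". Time-point comparisons follow only if the overall interaction is significant. Moderators are examined by adding a three-way interaction to the same model.

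The Design section gives the timing of T0: "After T0, the random assignment (with a ratio between DNK and CAU of 1:1) will be carried out by the first author", and "During the baseline measurement the participant, researcher and youth coach will still be blind to the treatment condition".

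Nothing in the text sets the two T0 means equal or makes T0 a covariate. The main analysis refers to adjusted means for Cohen's d, but names no covariate.

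**The concern.** With T0 as an outcome level and a full treatment × time structure, each arm has its own T0 mean. The T3 part of the interaction is then the mean change in DNK minus the mean change in CAU, which subtracts the chance T0 difference in full. Because T0 comes before randomisation, the data can instead show how much of T0 to subtract, and that estimate is more precise.

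The model serves the second aim of the study: development over time and moderation, for self-sufficiency and self-reported delinquency among others. Its overall test also decides whether any time point is examined. A loss of power there can hide a difference that the trial's own T3 comparison would show. The three-way moderator tests rest on the same mean structure.

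**Working it through.** **Inputs from the Power analysis section.** About 100 per arm at T3, "assuming an alpha of .05, a power of .80, and a small to medium effect size"; 34% follow-up dropout; 150 per arm; 40% loss in the effort period; 500 recruited.

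**Assumptions (not in the document).** Two-sided test; d = 0.40 at T3; a correlation ρ that is the same for every pair of visits, as a random participant intercept implies; equal variances; complete data. ρ is shown over a range.

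**The plan's own figures.**
- n per arm = 2(1.960 + 0.842)² / 0.40² = 98.1, so 99 (100 with the t distribution). The stated 100 is reproduced with d = 0.40.
- 100 / (1 − 0.34) = 151.5, so 152, against 150 planned.
- 300 / (1 − 0.40) = 500, as stated.

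**Variance of the T3 arm contrast, in units of 2σ²/n.**
- T3 alone: 1
- change from T0 (free T0 means, as planned): 2(1 − ρ)
- T0 as covariate: 1 − ρ²
- adjusted over planned: (1 − ρ²) / [2(1 − ρ)] = (1 + ρ)/2

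| ρ | planned | adjusted | ratio | reduction |
|---|---|---|---|---|
| 0.3 | 1.40 | 0.91 | 0.65 | 35% |
| 0.5 | 1.00 | 0.75 | 0.75 | 25% |
| 0.7 | 0.60 | 0.51 | 0.85 | 15% |

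**Power of the planned overall test (2 df).** With n = 100, nd²/2 = 100 × 0.16 / 2 = 8. For equal T2 and T3 effects the noncentrality is
- planned: 8 × 2 / [3(1 − ρ)], which is 7.62 at ρ = 0.3 and 10.67 at ρ = 0.5;
- T0 adjusted, joint test of the T2 and T3 effects: 8 × 2 / [(1 − ρ)(1 + 2ρ)], which is 14.29 and 16.00.

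The noncentral chi-square with 2 df gives:

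| T2 effect | ρ | planned | T0 adjusted |
|---|---|---|---|
| equal to T3 | 0.3 | .695 | .933 |
| equal to T3 | 0.5 | .841 | .957 |
| half of T3 | 0.3 | .562 | .792 |
| half of T3 | 0.5 | .718 | .853 |

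A simulation of fitted random-intercept models (200 runs per ρ, equal effects), with a common T0 mean as the adjusted version, gave .67 against .88 at ρ = 0.3, .845 against .965 at 0.5, and .965 against .99 at 0.7. The adjusted figure at 0.3 is below the formula; the ordering is the same throughout.

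**Against the T3 comparison.** T3 alone has power .807 at 100 per arm. The planned 2-df test falls below it when ρ is under about 0.46 (T2 effect equal to T3, or zero) or about 0.59 (T2 effect half of T3). At 150 per arm the values are about 0.44 and 0.58.

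**If T0 is less spread than T3.** Let k = SD(T0)/SD(T3). The change contrast then has factor 1 + k² − 2ρk, and T0 adjustment still gives 1 − ρ². At an assumed k = 0.7 and ρ = 0.3 these are 1 + 0.49 − 0.42 = 1.07 and 0.91, a reduction of 1 − 0.91/1.07 = 15% instead of 35%. The change contrast is then worse than T3 alone only when ρ is below k/2 = 0.35.

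**The case against.** The planned model is a standard and valid analysis, and it is labelled additional. The T3 comparison decides effectiveness, the sample size was set for T3, and moderation is exploratory. All of that stands, and it limits the point to one of efficiency.

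The size of the gain is uncertain. The document gives no ρ, and the Study sample section selects on low SSM-D scores, which may narrow the T0 spread of self-sufficiency. The gain is then smaller, as the k = 0.7 case shows. The post-hoc step can also be read as arm comparisons at each time point, so the overall 2-df test is the safer basis for power statements.

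A reader might infer that the planned model wastes T0, or is always weaker than the T3 comparison. It is not. At ρ = 0.7 with equal variances, its single T3 − T0 contrast has power .955 against .807 for T3 alone. What holds at every ρ below 1, under equal variances, is the loss against adjusting for T0.

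A reader might also infer that any T0 difference in the analysed data is chance, so that a common T0 mean can always be imposed. That holds for all randomised participants. The Design section, however, drops those who do not return after randomisation, about 40% expected, and the youth coach is told the allocation. Participants learn it only at the second interview, so arm-dependent return is not shown, but it is not excluded either. The second analysis keeps only those who started an intervention, after allocation is known. Forcing equal T0 means there could introduce bias. This part of the objection stands and shapes the fix. T0 as covariate does not force equal means, though in such sets it still needs the arms to be comparable given T0.

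**Conclusion.** The point holds as a loss of precision in a stated model. The treatment × time test compares changes from baseline and is less precise than a model adjusted for the pre-randomisation T0 value. The document does not support a claim of bias or of type I error inflation.

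The power cost at the planned size is substantial if ρ is low to moderate: about .70 against .93 at ρ = 0.3 and .84 against .96 at ρ = 0.5 for the overall test. It is small at ρ = 0.7. These figures rest on d = 0.40, a two-sided test, equal variances, complete data and equal T2 and T3 effects. The planned test falls below the plain T3 comparison only when ρ is under roughly 0.45 to 0.6, depending on the T2 effect.

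The scope is the development-over-time and moderator analyses of the continuous outcomes. Work/school has no T0 value in Table 1, and registered recidivism is analysed by Cox regression. No power figure was derived for the three-way moderator tests.

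**What to change.** - Model T2 and T3 as the outcomes, with treatment, time, treatment × time, T0 and T0 × time.
- Test the treatment effects at T2 and T3 jointly (2 df), then at each visit. In this model the treatment × time term alone asks only whether the effect differs between T2 and T3, so it must not replace the joint test.
- For moderators measured at baseline (demographic factors, SCIL, criminal history), test treatment × moderator at T2 and T3 with the same T0 adjustment. Motivation, group climate and alliance are measured after randomisation, and T0 adjustment does not make the arms comparable on them.
- Keep T0 as an outcome with a common mean only for the full randomised set. Do not use that version where non-returners or non-starters are excluded.

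The cost is a sentence or two in the analysis plan. Table 1 shows that T0 is already collected for every continuous outcome, so no new data or visits are needed.
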